## Materials and methods

### Purpose of the study

The study aims to identify key risk factors associated with differential survival and mortality outcomes in mechanically ventilated patients with moderate or severe ARDS who exhibit varying prognoses. This objective will be accomplished by investigating the differences and dynamic changes in clinical examinations, respiratory mechanics, lung ultrasound findings, and multi-omics analyses, as well as by further exploring their associations with prognosis. Additionally, the study aims to screen for functionally significant genes and candidate pathways, with a specific focus on lung injury-related mechanistic pathways, and identify the key immune cell subtypes (e.g., alveolar macrophages, T cell subsets, B cells, and myeloid cells) that determine the onset and prognosis of ARDS. Collectively, these efforts aim to provide novel insights and therapeutic targets to advance the precision treatment of ARDS.

### Study design

In this study, a prospective multicenter clinical cohort study will be conducted to observe the changes of lung injury, EIT, transpulmonary pressure, lung ultrasound, and other indexes in patients with ARDS. The effects on lung injury in patients with ARDS from the perspectives of respiratory mechanics, ventilation and perfusion, and lung imaging will be evaluated. The key indicators to provide clinical data support for the establishment of a 28-day death prediction model for patients with ARDS will be screened. The detailed technical route is shown in the following Fig 1. The specific sampling strategies and multi-omics detections were illustrated in Fig 2.

**Fig 1 pone.0332985.g001:**
[figure not shown]
Flowchart showing the study design. Eligible patient meets the inclusion and exclusion criteria and written informed consent will be enrolled. Baseline clinical data and biological samples will be collected immediately upon enrollment. Blood and BALF samples will be obtained on the first day of enrollment and prior to extubation. Throughout the study period, comprehensive clinical data, including laboratory test results, monitoring parameters, and treatment records, will be prospectively gathered. The 28-day clinical outcomes will also be documented. The collected samples will undergo multi-omics analyses, specifically transcriptomics, proteomics, metabolomics, and genomics. Clinical data will be further scrutinized using stratification analysis. Finally, all data will be integrated, and machine learning approaches will be employed to identify and characterize the key factors contributing to lung injury in ARDS patients undergoing invasive mechanical ventilation.

**Fig 2 pone.0332985.g002:**
[figure not shown]
Sample collection, pretreatment, and multi-omics analysis pipeline. A total of six multi-omics assays will be conducted, with sample utilization stratified by type and collection time point. Bronchoalveolar lavage fluid (BALF) samples collected within 24 hours of enrollment will first utilize the original fluid for clinical mNGS for pathogen diagnosis, alongside metagenomic microecology analysis and virus spectrum analysis. All samples will undergo centrifugation within 24 hours of collection. Following centrifugation, the BALF supernatant will be subjected to proteomic and metabolomic assays, while the resulting cell pellet will be utilized for transcriptomic and single-cell transcriptomic analyses. Concurrently collected blood samples will also be centrifuged, with the plasma used for proteomic and metabolomic assays, and peripheral blood mononuclear cells (PBMCs) utilized for bulk transcriptomic and single-cell transcriptomic analyses. For the late phase, BALF and blood samples collected prior to extubation (with priority given to day 10 ± 2) will focus on transcriptomic and single-cell transcriptomic analyses: centrifugation-derived BALF cell pellets and blood PBMCs will be exclusively used for these assays.

### Participant recruitment

Participants will be recruited from ten medical centers in tertiary general hospitals in North China, including the First Medical Center of Chinese PLA General Hospital, the Sixth Medical Center of Chinese PLA General Hospital, the Eighth Medical Center of Chinese PLA General Hospital, Beijing Shijitan Hospital, Beijing Anzhen Hospital, AMHT Group Aerospace 731 Hospital, Zhengzhou Central Hospital, Henan Provincial People’s Hospital, the First Affiliated Hospital of Zhengzhou University and First Hospital of Shanxi Medical University.

Patients with ARDS will be invited to participate in this study upon admitting the branch center. Those who meet the inclusion criteria and provide signed informed consent will enter the screening period (S1 File). During the screening visit, trained researchers (physicians) will confirm the eligibility based on symptoms, laboratory results, and chest X-ray or CT image, and review every inclusion and exclusion criterias. Patients who meet the exclusion criteria will be excluded from this study within 24 hours. The recruitment period is set for 24 months, spanning from November 2023 to November 2025.

### Inclusion and exclusion criteria

In this study protocol, patients with moderate or severe ARDS and experienced mechanical ventilation will be included for inclusion selection. The definition of ARDS refers to the Berlin definition of ARDS [3]. The core diagnostic criteria include: an onset time within 1 week after a known clinical insult or the onset of new/worsening respiratory symptoms; chest imaging findings of bilateral lung opacity or patchy shadows that cannot be fully explained by conditions such as pleural effusion, atelectasis, or nodules; respiratory failure that cannot be fully attributed to heart failure or fluid overload, with objective examinations such as echocardiography required to rule out hydrostatic pulmonary edema in the absence of clear predisposing risk factors; and disease severity classified into three grades based on the oxygenation index (PaO₂/FiO₂) combined with a positive end-expiratory pressure (PEEP ≥ 5 cmH₂O): mild (200 mmHg < PaO₂/FiO₂ ≤ 300 mmHg, with continuous positive airway pressure ventilation permitted), moderate (100 mmHg < PaO₂/FiO₂ ≤ 200 mmHg), and severe (PaO₂/FiO₂ ≤ 100 mmHg). Patients with moderate or severe ARDS will be included.

Patients meeting any of the following criteria will be excluded from the study:

Patients aged less than 18 years old.Patients with intracranial hypertension, acute coronary syndrome, pleural fistula, pneumothorax, and subcutaneous emphysema.Pregnant and lactating patients.Patients with severe hemodynamic instability (vasopressor dose increased by >30% within the first 6 hours, or noradrenaline dose > 0.5 μg/kg/min).Patients who do not agree to participate in this study and patients do not sign the informed consent.

### Data collection

The formal baseline data and serial data of the participants will be collected. Three case report forms (CRFs) have been designed for different stages of patient enrollment management (S2–S4 Files).

The formal baseline data includes the following aspects:

Demographic data: hospitalization number, name, sex, age, main cause of admission, ethnicity, smoking history, and body mass index.

Medical history: hypertension, coronary heart disease, diabetes, kidney disease, hepatopathy, cerebrovascular disease, autoimmunity disease, hemopathy, pulmonary disease, and cancer.

Medication use within 28 days: antibiotics, hormones and immunosuppressants, vasoactive agent, neuromuscular blockers, sedative and analgesic drugs.

Physical examination findings: blood pressure, pulse rate, heart rate, respiratory rate, and temperature.

Severity scores: the Acute Physiology and APACHE II and the SOFA score.

Mechanical ventilation parameters (on day 1 and before extubation): ventilation mode, inhaled oxygen fraction, PEEP, frequency, tidal volume, flow rate, expiratory tidal volume, peak pressure, plateau pressure, airway resistance.

Respiratory mechanics (on day 1 and before extubation): the respiratory system compliance (C_rs_), static compliance of the lungs (C_lung_), respiratory system airway resistance (R_rs_), esophageal pressure (P_es_), transpulmonary pressure (P_tp_), transpulmonary driving pressure (△P_tp_), driving pressure (△P), dead space fraction (V_D_/V_t_) and mechanical power (MP).

Cardiac echocardiography (on day 1 and before extubation): measurement of left ventricular ejection fraction.

Pulmonary ultrasound score and pulse indicator continuous cardiac output parameters.

Serial data: The serial data will be collected on days 1, 3 ± 1, 7 ± 1, 14 ± 2, 21 ± 2, 28 ± 2, and before extubation, discharge or death, including inflammatory markers (white blood cell count, neutrophil count and proportion, interleukin-6, C-reactive protein, procalcitonin, etc.), arterial blood gas, coagulation, blood glucose, blood lipids, electrolytes, myocardial enzymes, immune indicators, BALF tests (cell count, classified examination and etiological examination).

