**Methods/Design:**

We designed a prospective multicenter cohort study incorporating multi-omics analyses. This research aims to investigate the mechanisms underlying the development and progression of ARDS during mechanical ventilation, providing a theoretical foundation and practical guidance for future ARDS therapies. The study plans to enroll over 165 patients with moderate to severe ARDS receiving mechanical ventilation across 10 medical centers. Peripheral blood and bronchoalveolar lavage fluid (BALF) samples will be collected on the first 24 hours after enrollment and at extubation for metagenomic/meta-transcriptomic sequencing, bulk RNA sequencing, single-cell RNA sequencing, proteomics detection, and metabolomics analyses. Concurrently, comprehensive monitoring of physiological indices, electrical impedance tomography, transpulmonary pressure, pulmonary ultrasound findings, and other relevant parameters will be conducted during the enrollment. Study participants will be stratified by survival and mortality outcomes to analyze the dynamic trends of all measured indices and their underlying molecular mechanisms. Biomarkers derived from multi-omics data and clinical baseline characteristics will be evaluated and integrated, followed by multidimensional dimensionality reduction. Predictive models will be subsequently constructed via early or late fusion to identify core prognostic markers, with performance validated using standardized metrics.

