### Follow‑up schedules

At the 28-day mark, patients will be assessed for the primary outcome of survival or death. At this point, the attending physician will report the primary outcome, and the data collection database will then document the 28-day mortality rate, as well as the duration of ICU and hospital stays, along with other relevant outcomes. During the study period, specific measurements will be taken at predetermined time points: day 1, day 3 ± 1, day 7 ± 1, day 14 ± 2, day 21 ± 2, day 28 ± 2, and before extubation (with priority to day 10 ± 2), discharge or death. The following parameters will be recorded: inflammatory markers, arterial blood gas, coagulation, blood glucose, blood lipids, electrolytes, myocardial enzymes, immune indexes, cell count and classification of BALF and etiological examination. 28-day administration of antibiotics, neuromuscular blockers, vasoactive agent, hormones and immunosuppressants will be tracked. The measurement and collection schedule of this experiment are summarized in the follow-up form (Table 1).

**Table 1 pone.0332985.t001:** The schedule of measurements and visits of this trial.

Timeline (day)	Screening	Follow-up								
	d1	d3 ± 1	d7 ± 1	before extubation (priority: d10 ± 2)	d14 ± 2	d21 ± 2	d28 ± 2	discharged/death (≤28 days)	d1-28	d28
**Informed consent form**	Χ									
**Inclusion/exclusion criteria**	Χ									
**Demographic data**	Χ									
**History of diseases**	Χ									
**ARDS risk factors**	Χ									
**Clinical symptom**	Χ	Χ	Χ	Χ	Χ	Χ	Χ	Χ		
**Imaging**	Χ	Χ	Χ	Χ	Χ	Χ	Χ	Χ		
**APACHE Ⅱ scores**	Χ	Χ	Χ	Χ	Χ	Χ	Χ	Χ		
**SOFA scores**	Χ	Χ	Χ	Χ	Χ	Χ	Χ	Χ		
**mechanical ventilation parameter**	Χ	Χ	Χ	Χ						
**respiratory mechanics**	Χ			Χ						
**pulmonary ultrasound score**	Χ			Χ						
**cardiac echocardiography**	Χ			Χ						
**pulse indicator continuous cardiac output parameters**	Χ			Χ						
**mNGS detection**	Χ									
**Clinical pathogen detection**	Χ	Χ	Χ	Χ	Χ	Χ	Χ	Χ		
**Laboratory examination**	Χ	Χ	Χ	Χ	Χ	Χ	Χ	Χ		
**BALF cell count and classified examination**	Χ			Χ						
**Samples**	Χ			Χ						
**Antibiotic use record**									Χ	
**vasoactive agent use record**									Χ	
**neuromuscular blockers, sedative and analgesic drugs use record**									Χ	
**Adverse events**									Χ	
**28-day survival follow-up**										Χ
**28-day ICU length of stay**										Χ
**28-day ventilator-free days**										Χ

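### Post-enrolment data are filed as baseline, and no prediction time is set to keep them out of the 28-day mortality model

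*Protocol article*

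**What the plan says.** The Data collection section opens its first list with "The formal baseline data includes the following aspects". That list contains:

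- "Medication use within 28 days: antibiotics, hormones and immunosuppressants, vasoactive agent, neuromuscular blockers, sedative and analgesic drugs"
- "Mechanical ventilation parameters (on day 1 and before extubation")
- "Respiratory mechanics (on day 1 and before extubation")
- "Cardiac echocardiography (on day 1 and before extubation")

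A separate paragraph in the same section covers serial data, so the article does distinguish baseline from follow-up.

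Two other places bear on timing. Follow-up schedules says "28-day administration of antibiotics, neuromuscular blockers, vasoactive agent, hormones and immunosuppressants will be tracked", and Table 1 enters the drug-use records only in the column for days 1 to 28. The Fig 1 legend says "Baseline clinical data and biological samples will be collected immediately upon enrollment".

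On use of the data, the abstract (Methods/Design) says "Biomarkers derived from multi-omics data and clinical baseline characteristics will be evaluated and integrated", after which predictive models are built. Study design says that key indicators will be screened for a 28-day death model. Statistical analysis specifies a Cox model for 28-day mortality. Sample size calculation sets the hypothesis of an AUC of at least 0.85, tested against 0.70. The multi-omics section makes an AUC of 0.85 or more a key criterion of clinical utility.

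**The concern.** A model meant to predict death by day 28 from the start of the study may use only what is known at the start. Drug exposure counted over follow-up is cut short by death, so fewer drug-days can simply mean an earlier death. A late physiological value is missing for patients who die before it is due. Used as fixed covariates, both carry information about survival itself.

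The article's definition of baseline admits such items, its modelling route takes in baseline characteristics, and no stated time limit stops them. The resulting AUC could look better than the model's true performance, and the model could not be applied to a patient on day 1. Holding out patients or centres would not reveal this, because the held-out records are built under the same definitions.

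**Working it through.** **1. Timing of the items listed as baseline**

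| Item | Data collection | Elsewhere |
|---|---|---|
| Drug use | within 28 days, direction not stated | Follow-up schedules: 28-day use is tracked; Table 1: days 1-28 column only |
| Ventilation, mechanics, echocardiography | day 1 and before extubation | Table 1: day 1 and pre-extubation columns (ventilation also days 3 and 7) |
| Baseline data in general | includes all of the above | Fig 1 legend: at enrolment |

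The drug classes in Follow-up schedules (antibiotics, neuromuscular blockers, vasoactives, hormones and immunosuppressants) and in Table 1 (which adds sedatives and analgesics) together cover every class in the baseline line. Table 1 schedules no day-1 medication record. This favours reading the 28 days as follow-up.

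**2. The plan's own figure.** 66 deaths / 0.40 = 165 patients, as stated. The 66 can be matched by a two-sided binormal calculation with equal groups: 59 deaths, and 59 / 0.90 = 65.6, rounded up to 66. The article does not name that variant. Nothing in this point disputes the figure.

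**3. Drug exposure (illustration).** Only the 40% mortality comes from the article; the rest is assumed. The hazard is constant at −ln(0.60)/28 = 0.0182 per day. The drug is given on a random fraction p of days alive, unrelated to risk, so the honest AUC is 0.50. Exposure is counted to death or day 28, and fewer days are taken to predict death.

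| p | AUC, cumulative days | AUC, any use yes/no |
|---|---|---|
| 0.02 | 0.61 | 0.60 |
| 0.05 | 0.69 | 0.66 |
| 0.10 | 0.76 | 0.64 |
| 0.20 | 0.83 | 0.58 |
| 0.50 | 0.91 | 0.52 |

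A second simulation used one course per patient, with an exponential intended duration capped at 28 days and observed days = min(intended, day of death). Mean durations of 7, 14 and 28 days gave cumulative-day AUCs of 0.55-0.60, 0.61-0.69 and 0.70-0.78; the ranges cover uniform and front-loaded death times. A drug given without a break until death or day 28 gave about 0.97-0.98, which is an extreme case.

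**4. Late values.** The sampling section takes late samples on days 7-14 from patients not yet extubated, and Table 1 gives the pre-extubation column a day 10 ± 2 priority. Mainly early deaths would therefore lack a late value. Under the same constant hazard, the share of 28-day deaths that occur

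- before day 7 is (1 − 0.60^(7/28))/0.40 = 0.120/0.40 = 0.30;
- before day 14 is (1 − 0.60^(14/28))/0.40 = 0.225/0.40 = 0.56.

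If availability itself acted as a predictor, AUC = 0.5 + (availability in survivors − availability in deaths)/2. Assuming 90-95% of survivors and 40-70% of deaths have a value:

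- lowest: 0.5 + (0.90 − 0.70)/2 = 0.60
- highest: 0.5 + (0.95 − 0.40)/2 = 0.78

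Assuming 50-90% and 5-20% instead gives 0.65 to 0.93. The article anchors neither pair.

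**5. Omics.** The Fig 2 legend sends late samples only to bulk and single-cell transcriptomics. Proteomics, metabolomics and metagenomics come from the first sample, so only late transcriptomic data could leak.

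**The case against.** The strongest reply is that Data collection lists what is recorded, not what enters the model. The list even includes name and hospitalisation number. No section says that 28-day drug use or a pre-extubation value is a predictor. The model-building text in the multi-omics section names only omics layers, and Statistical analysis names no covariates. The final predictor list may properly sit in an analysis plan that is not shown. This stands: a reader might infer that the planned predictors already encode the outcome, and the article does not support that.

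The medication line, placed between medical history and physical examination, could also mean drugs taken before enrolment. Read alone, it could. Follow-up schedules and Table 1 point the other way, and if prior use was meant the line needs to say so. The pre-extubation items have no such alternative reading.

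A reader might further infer that late values exist only in extubated patients, or that the transcriptomic layer will mix early and late samples. The day 7-14 rule contradicts the first. On the second, the multi-omics section says that RNA-seq is meant to capture early host responses, although it does not expressly exclude late samples.

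Finally, the large AUCs need cumulative-day coding, or missingness acting as a predictor. The article proposes neither.

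What survives is more than absent detail. The article defines baseline in a way that contradicts its own Fig 1 legend and names baseline characteristics as model input. An analysis plan that said only baseline covariates would inherit the error.

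**Conclusion.** The point holds in conditional form. Items measured after enrolment are filed as baseline, in conflict with the Fig 1 legend, and no prediction time, landmark or time-dependent handling keeps them out of the 28-day mortality model. If the baseline set is used as listed, the AUC can be inflated and the hold-out would not show it.

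The size cannot be fixed from the article. In the random-daily-use illustration it is small to moderate for any-use coding (0.52-0.66 against an honest 0.50) and can be large for cumulative drug-days (0.61-0.91). Some of these scenarios pass the 0.70 null, and a few pass 0.85, with no prognostic content. These figures rest on assumed usage, coding and availability; they show what could happen and do not forecast this study's result. Whether the leak occurs depends on a predictor list that the article does not give.

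**What to change.** - Reconcile Data collection, the Fig 1 legend and Follow-up schedules: move 28-day medication use and all pre-extubation values to follow-up data. If medication before enrolment is also wanted, list it as a separate, clearly dated item.
- State in the multi-omics section and in Statistical analysis that every predictor in the 28-day mortality model (clinical, physiological and omics) is measured no later than 24 h after enrolment. This also excludes late RNA-seq and scRNA-seq.
- Analyse late samples and 28-day drug exposure descriptively, or in a separate landmark analysis of patients alive at the landmark day.

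The cost is a wording change and a date filter on data already being collected; day-1 values are recorded separately. The 66 deaths and 165 patients do not change. The downside is that the reported AUC may be lower.

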### Data management

In this protocol, we employ a web-based CRF data management system (DMS) for data collection and centralized management throughout the experiment. The DMS records patients’ enrollment details, clinical treatment data, and sample collection information (e.g., time, location, handling procedures), enabling full-lifecycle patient data management, including screening and real-time monitoring of adherence to predefined inclusion/exclusion criteria. After new participants are enrolled, data collectors will visit sub-centers weekly to input required information into the online DMS (https://h6world.cn). The data administrator is responsible for collecting data monitored by independent external supervisors. Questions or outliers should be answered by the quality control officer. 10% of the subjects will be randomly selected and tested with the original questionnaire to evaluate the bit error rate. Based on the bit error rate, the subsequent monitoring plan will be arranged. If an error occurs, the incorrect data in the database must be corrected and all modifications must be documented in the DMS. Once data entry and resolution of issues are complete, the research data will be locked by the lead researcher, preventing any further alterations by the researchers. No compensation will be provided.

### Sample collection, and multi-omics profiling

For enrolled patients, peripheral blood and BALF samples will be collected at two time points: within 24h after enrollment and before tracheal extubation. For patients who cannot be extubated within 7–14 days, samples will be collected during this 7–14 day window, with priority given to day 10 ± 2 (Fig 2).

For blood sampling, patients must be in a fasting state prior to blood collection. A total of 10–15 mL of blood will be collected using anticoagulant tubes, which will then undergo pretreatment before separate storage or detection. Within four hours of sampling, centrifugation will be conducted at 3000 r/min for 10 minutes. The resulting plasma will be aliquoted into 1.5 mL EP tubes at 500 μL per tube for subsequent proteomics and metabolites detection. For the remaining sample, equal volumes of phosphate buffered saline (PBS) and Ficoll lymphocyte separation solution will be added, followed by centrifugation at 1000g for 20 minutes to collect PBMCs. After adding 5 mL of PBS, the mixture will be centrifuged at 400g for 5 minutes, the supernatant will be discarded, and PBMCs will be resuspended in cell cryopreservation solution before aliquoting into EP tubes at 1 mL per tube. The PBMC samples will be used for RNA-seq and scRNA-seq. The samples will be stored at −80°C before multi-omics detection.

For BALF sampling, two tubes of BALF samples will be collected. One tube, containing no less than 10 mL, will undergo pretreatment for subsequent RNA-seq, scRNA-seq, proteomics and metabolites detection. The other tube, with a volume of at least 5 mL, will be directly submitted for clinical mNGS pathogen testing, as well as for metagenomic microbial spectrum analysis and meta-transcriptomic expression profiling. For reserved samples, 6 mL of BALF will be centrifuged at 4000g for 10 minutes. The supernatant will then be aliquoted into 1.5 mL EP tubes at 400 μL per tube, while 1 mL of Trizol will be added to the remaining cell pellet, followed by vortex mixing. All aforementioned samples, along with the remaining BALF, will be labeled and stored at −80°C. The supernatant will be used for proteomics and metabolites detection, while the bottom cell-sedimentation will be used for bulk RNA-seq and scRNA-seq. Since BALF sampling is invasive, the patient’s condition will be evaluated prior to sampling. If the attending physician determines that further sampling is inappropriate or the patient declines sampling, the procedure will not be performed. During sampling, certain adverse events will be documented. Subsequently, the attending physician will assess the feasibility of subsequent sampling. If the risk of further BALF sampling is deemed relatively high, the patient will be excluded from the study.

BALF samples collected for mNGS-based infectious disease diagnosis will be transported immediately to the corresponding testing center for mNGS pathogen detection. Any samples that could not be shipped on the day of collection should be temporarily stored at 2–8°C. Other collected samples will underwent appropriate preprocessing before being preserved at −80°C. Following the enrollment of all patients, all samples will be uniformly transported to the PLA General Hospital via cold chain logistics for multi-omics analysis. Crucially, all samples will be subjected to no more than one freeze-thaw cycle prior to testing to maintain sample integrity. The detailed methods for multi-omics detections are summarized in S5 File.

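### For measures taken only on day 1 and before extubation, the day and clinical state of the second value depend on the course of illness, so survivor-versus-death trends in them are confounded and omit early deaths

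*Protocol article*

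**What the plan says.** The section on sample collection and multi-omics profiling sets the rule: "peripheral blood and BALF samples will be collected at two time points: within 24h after enrollment and before tracheal extubation". An alternative follows for patients who stay on the ventilator: "For patients who cannot be extubated within 7–14 days, samples will be collected during this 7–14 day window", with day 10 ± 2 preferred. The Fig 2 legend, Follow-up schedules and Outcomes repeat this scheme in whole or part.

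The Fig 2 legend limits what the late sample is used for: "BALF and blood samples collected prior to extubation (with priority given to day 10 ± 2) will focus on transcriptomic and single-cell transcriptomic analyses", and "centrifugation-derived BALF cell pellets and blood PBMCs will be exclusively used for these assays". Proteomics, metabolomics and metagenomics therefore come from the first sample only.

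Table 1 gives the same two-point schedule (day 1 and before extubation, nothing at discharge or death) to samples, respiratory mechanics, lung ultrasound, echocardiography, pulse-indicator cardiac output parameters and BALF cell counts. The Data collection text lists BALF cell counts with the serial data, but Table 1 marks them only twice. Laboratory tests, imaging, SOFA and APACHE II are marked on every scheduled day and at discharge or death.

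The Abstract states the planned comparison: "Study participants will be stratified by survival and mortality outcomes to analyze the dynamic trends of all measured indices and their underlying molecular mechanisms". The Purpose section makes dynamic changes and their link with prognosis part of the objective. There is one further route of loss: "If the risk of further BALF sampling is deemed relatively high, the patient will be excluded from the study".

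**The concern.** Whether a patient is about to be extubated, is still ventilated in the second week or has already died is closely tied to 28-day survival, which is the grouping variable. The same feature decides when, in what state and whether the second value is obtained. A survivor-versus-death difference in a late value, or in its change from day 1, can then arise in three ways unrelated to a prognostic mechanism:

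- the groups were sampled after different numbers of ventilated days;
- one group was sampled at readiness for extubation and the other was not;
- the non-survivors with a second value are only those who lived long enough to give one.

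At stake are the late transcriptomic and physiological findings, which the Discussion presents as a strength of the two-time-point design. The limitations do not mention this problem. A second, conditional stake is the mortality model. Study design draws its candidate indicators from respiratory mechanics, ultrasound and similar measures, and the integration section feeds in transcriptomic features without naming a time point. If late values entered the model, they would partly encode recovery.

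**Working it through.** **1. The plan's own figures.** 66 deaths / 0.40 mortality = 165 patients; at the target of 200, 200 × 0.40 = 80 deaths. The 66 is reproduced by a binormal variance for AUC 0.85 against 0.70, two-sided 5%, 90% power and equal groups: 59 deaths, and 59 / 0.90 = 65.6, rounded up to 66. Those settings are inferred, not stated. The present point does not depend on them, but 66 counts every death, whether or not a second sample exists.

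**2. Three hypothetical patients under the rule.**

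| Course | Second value | State when taken |
|---|---|---|
| Ready for extubation on day 5 | day 5 | recovering |
| Still ventilated on day 10 | day 10 | not ready for extubation |
| Dies ventilated on day 4 | none | – |

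The first course is typical of survivors; the other two are commoner among deaths. The overlap is partial: some survivors are still ventilated in days 7–14, and some extubated patients die later.

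**3. Deaths without a second value.** The documents give no timing of deaths, so the share before the second sample is an assumption of 20–40%.

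- Of 66 deaths: 66 × 0.20 = 13 and 66 × 0.40 = 26 lost, leaving 53 to 40.
- Of 80 deaths: 80 × 0.20 = 16 and 80 × 0.40 = 32 lost, leaving 64 to 48.

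**4. Size of the sampling-day effect (all inputs assumed).** Take a marker unrelated to death that drifts 0.05, 0.10 or 0.15 SD per ventilated day, with mean sampling days 4 apart. The spurious difference is d = drift × 4 = 0.2, 0.4 or 0.6 SD. With 90 survivors and 40 non-survivors sampled, z = d × √(90 × 40 / 130) = d × 5.26, and the rejection rate of a nominal 5% test is P(|Z + z| > 1.96).

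| d | z | Rejection rate |
|---|---|---|
| 0.2 | 1.05 | 18% |
| 0.4 | 2.10 | 56% |
| 0.6 | 3.16 | 88% |

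A simulation with other assumptions put survivors at mean day 6, 7 or 8 and non-survivors at mean day 10, with 99 survivors and 40 deaths. At a drift of 0.10 SD per day the rejection rates were 55%, 35% and 18%. At mean day 6 with drifts of 0.05 and 0.20 they were 19% and 98%. Over these cases the null marker's AUC ran from about 0.55 to 0.70. With equal mean days the rejection rate returned to about 5%.

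**5. What the arithmetic leaves out.** It covers sampling day only. The difference between patients ready and not ready for extubation is not quantified, and it remains even when both are sampled on the same day.

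**The case against.** Four arguments stand on the other side.

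*An analysis plan could deal with it.* The article is condensed, sampling times are recorded in the data management system, and adjustment for day is ordinary analysis-plan content. Silence on covariates is indeed no fault here. But adjustment for day does not separate readiness for extubation from prognosis, and no analysis recovers samples that early deaths never gave. The problem lies in what the article fixes: the sampling rule together with the survivor-versus-death trend comparison.

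*Day 10 ± 2 has priority.* This narrows the spread, and survivors still ventilated share the window with non-survivors. It is a preference, and extubation before day 8 still sets an earlier sample. The 4-day gap used above has no source in the documents.

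*Early deaths are missing from all trends.* A reader might infer this from the Abstract's reference to all measured indices. The documents do not support it. Laboratory values, imaging, SOFA and APACHE II are also taken on fixed days and at discharge or death, so early deaths contribute until they die. Ventilator settings are also recorded on days 3 and 7.

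*The mortality model's AUC will be inflated.* This too is a tempting reading that goes too far. No section says late values enter the model. The late sample serves transcriptomics only, and the integration section speaks of day 1, baseline and early responses. What stands is that nothing excludes late transcriptomic, mechanics or ultrasound values.

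**Conclusion.** The point holds for the two-point measures. As planned, their survivor-versus-death trends are confounded by sampling day and extubation readiness and leave out early deaths. The direction follows from the documents alone; the size does not. The loss of 13–26 of 66 deaths assumes that 20–40% of deaths come before the second sample. The 18–88% false-positive rates assume a drift, a sampling-day gap and group sizes that the documents do not give, and they fall to about 5% if the mean sampling days are equal.

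For the mortality model the conclusion is conditional. If late values were used, the AUC judged against 0.85 could be inflated and would not describe prediction at enrolment.

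The primary outcome, the sample size calculation and all day-1 omics are unaffected. The affected RNA analyses are listed as additional outcomes in a study that calls itself exploratory, but they serve the stated aim of explaining dynamic changes.

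**What to change.** - **Model.** State that the 28-day mortality model uses day-1 predictors only.
- **Late values.** Analyse those taken at actual extubation separately from those taken in the day 7–14 window while still ventilated. Within the window group, start follow-up at the recorded sampling day and relate the late value, and its change from day 1, to death from then to day 28, adjusting for sampling day. Both parts are needed: the split handles extubation readiness, the adjustment handles timing.
- **Reporting.** Give the number of deaths without a second sample, and limit conclusions from late values to patients who reached one.

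The cost is analysis wording: no change in sampling or clinical care, and sampling times are already recorded. The price is fewer deaths in the late-value analyses (53 to 40 of 66 in total under the assumed range, before the split into two groups) and a narrower question: prognosis among those still ventilated at the second sample, not among all enrolled patients.
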